## Abstract

**Background:**

Diminished ovarian reserve (DOR) is the precursor state of ovarian failure and can cause the decline of women’s reproductive function. DOR also leads to poor outcome of in vitro fertilization and embryo transfer (IVF-ET) by affecting the oocytes, high qualified embryo rate, pregnancy rate, etc. Some studies have demonstrated that acupuncture can improve ovarian function. But to date, there is limited evidence indicating that acupuncture or electro-acupuncture is efficient to DOR. This trial aims to evaluate the efficiency and safety of electro-acupuncture for the ovarian function and the following outcome of IVF-ET in DOR patients.

**Methods:**

This will be a multicenter randomized controlled clinical trial. A total of more than 338 women with DOR will be randomly allocated to treatment and control groups in 1:1 ratio receiving acupuncture before undergoing IVF-ET. The primary outcome will be the clinical pregnancy rate per cycle of IVF-ET after acupuncture. The secondary outcomes will be ovarian reserve function, outcomes of IVT-ET, blood biochemical index, Massachusetts General Hospital Acupuncture Sensation Scale (MASS), scores from the self-rating anxiety and depression scale, quality of life, and pregnancy outcomes. The safety of acupuncture will also be assessed.

**Discussion:**

The results of this trial may provide high-quality evidence regarding the effectiveness of electro-acupuncture in the treatment of DOR and following outcomes of IVF-ET. This will also help patients with DOR and their physicians by offering a new treatment option.

**Trial registration:**

Chinese Clinical Trial Registry ChiCTR1900024626. Registered on 19 July 2019.

**Supplementary Information:**

The online version contains supplementary material available at 10.1186/s13063-021-05894-2.

## Background

Diminished ovarian reserve (DOR) indicates a reduced number of retrieved follicles and the reduction of the quality of oocytes affected by non-biological reasons before the age of 40. Multiple studies consider that the cause of DOR is related to age, genetic factors, immune factors, social and environmental factors, infection, iatrogenic injuries, multiple pregnancies, etc. Normally, the ovarian reserve function declines at the age of 30, and fall off sharp after 35. The incidence rate of DOR is climbing and shows a younger trend. However, there is no effective pharmacotherapy at present.

In-vitro fertilization-embryo transfer (IVF-ET) is a main therapy treating infertility, and controlled ovarian hyperstimulation (COH) is the key step. In IVF-ET, the success of COH depends on the ovarian reserve function and ovarian response. A clinical trial finds that when undergoing IVF-ET, the DOR patients’ initial dose of gonadotropin (Gn), total Gn, Gn days, and abortion rate are obviously higher than patients with normal ovarian function, but the oocytes, M II oocytes rate, high qualified embryo rate, fertilization rate, implantation rate, and pregnancy rate are all distinct inferior to patients with normal ovarian function [1]. In addition, DOR can cause reproductive endocrine dysfunction including less menstrual volume, menstrual loss, and amenorrhea, which further affects women’s reproductive function. Besides, it also leads to perimenopause-related symptoms, such as hot flashes, night sweats, irritability, etc. All these symptoms impact on patients’ quality of life. And it will develop into premature ovarian failure (POF) within 1–6 years when without intervention at an early stage. Hence, a new therapy for DOR is necessarily required.

In recent years, as an important part of traditional Chinese medicine, acupuncture has attracted tons of attention in the fields of reproductive endocrine and infertility worldwide [2–4]. Acupuncture can stimulate the neuro-endocrine system, regulate the overall endocrine level and ovarian microenvironment as a whole, improve the internal environment of follicles, improve ovarian hemodynamics, and thereby promote follicular development and ovulation. In addition, acupuncture can also enhance endometrial receptivity and relieve patients' tension and anxiety in assisted reproductive technology (ART) [5]. Acupuncture, which can improve ovarian function, is now widely used in the treatment of POF. Two Meta-analysis show that acupuncture is a relative effective intervention treating POF, which helps for recovering menstruation and boosting level of serum follicle-stimulating hormone (FSH) and estradiol (E2). The curative is sustainable till a month after the end of treatment [6, 7]. Since DOR can develop to POF within 1–6 months, why do not we intervene it in the early DOR phase in order to delay or reverse the progress to POF?

Given its effect on ovarian function, acupuncture is expected to be a new option for the treatment of DOR. But to date, the available evidence of the efficacy of acupuncture or electro-acupuncture for DOR remains insufficient. Only a few small sample, non-randomized controlled clinical trials suggest that acupuncture or electro-acupuncture can improve ovarian reserve function of DOR patients [8, 9]. Therefore, a large sample, multicenter, randomized controlled trial is designed to evaluate the efficiency and safety of electro-acupuncture in DOR patients. The clinical pregnancy rate is the primary outcome reflecting ovarian function. The following outcome of IVF-ET will also be evaluated as a secondary outcome.

### Objectives

Through this study, we expect to test the following hypotheses: (1) evaluate whether electro-acupuncture is superior to the control group in ameliorating ovarian function of DOR patients reflected by improving clinical pregnancy rate, and (2) assess the safety of electro-acupuncture.

## Methods

### Trial design

This will be a multicenter, randomized, controlled clinical trial. The trial was designed as a superiority trial, with the aim of evaluating whether the electro-acupuncture intervention was superior to the control group in improving ovarian function of DOR patients. A total of more than 338 women with DOR will be randomly allocated to treatment and control groups in 1:1 ratio receiving acupuncture before undergoing IVF-ET.

This trial has been registered at the Chinese Clinical Trial Registry (ChiCTR1900024626). The flowchart and study design schedule are presented in Fig. 1 and Table 1. The Standard Protocol Items: Recommendations for Interventional Trials (SPIRIT) checklist is provided as Additional file 1.

**Fig. 1 Fig1:**
[figure not shown]
Flowchart of the trial procedures

**Table 1 Tab1:**
[figure not shown]
Participants timeline

*AFC* antral follicle count, *AMH* anti-Müllerian hormone, *IVF-ET* In-vitro fertilization-embryo transfer, *MASS* Massachusetts General Hospital Acupuncture Sensation Scale, *AEs* adverse events

### Study setting

Patients will be recruited from the following 4 hospitals in China: Tongji Hospital affiliated to Tongji Medical College of Huazhong University of Science and Technology, Union Hospital affiliated to Tongji Medical College of Huazhong University of Science and Technology, Wuhan First Hospital, and Reproductive Hospital affiliated to Jiangxi University of Traditional Chinese Medicine.

### Consent to participate

This protocol is in accordance with the principles of the Declaration of Helsinki. Written informed consent will be obtained from patients prior to enrolment. The informed consent is provided as Additional file 2. In each sub-center, two independent gynecologists are responsible for recruiting patients and gaining informed consent. On the consent form, participants will be asked if they agree to the use of their data when they choose to withdraw from the trial. Participants will also be asked for permission for the research team to share relevant data with researchers from the universities taking part in the research or from regulatory authorities, where relevant. This trial does not involve collecting biological specimens for storage. No changes are made to the trial protocol after the subject recruitment started.

### Inclusion criteria

Participants will be included if they meet the following criteria: (1) age < 40, will undergo IVF-ET; (2) low ovarian reserve: antral follicle count (AFC) < 7, or AMH< 1.1 ng/ml; or has a history of poor ovarian response: in the last hyperstimulation cycle, the number of retrieved oocytes < 3; (3) spouse’ semen examination is normal, or after semen prewash can reach the standard of common IVF or intracytoplasmic sperm injection (ICSI).

### Exclusion criteria

Participants will be excluded if they meet any of the following criteria: (1) male with azoospermia; (2) male/female’s chromosome is abnormal; (3) adenomyosis, uterine fibroids, endometrial polyps, scar uterine, reproductive system tuberculosis, oviduct effusion, pelvic lesions such as ovarian endometriosis cyst or tumor; (4) female has other endocrine diseases: thyroid diseases, hyperprolactinemia, insulin resistance, diabetes, adrenal diseases, etc.; (5) definitively diagnosed autoimmune diseases such as systemic lupus erythematosus, rheumatoid arthritis, and antiphospholipid syndrome; (6) other pathogenesis that leads to recurrent miscarriage or agnogenic recurrent miscarriage; (7) a history of cancer and has received radiotherapy and chemotherapy; (8) had acupuncture treatment in recent 3 months; and (9) unwilling to sign the informed consent of this study.

### Randomization and masking

Internet-based central randomization system will be applied in this trial. Three hundred thirty-eight participants will be randomly allocated to the treatment group and control group in a 1:1 ratio. The Internet-based central randomization system designs the random parameters and allocation. The appointed researchers in each hospital will apply for the group assignment allocated by the system through inputting a specific code. The randomization protocol and the parameters set during it are collectively called blinding code, which are kept strictly by researchers who are not involved in the process of outcome evaluation and statistical analysis.

### Interventions

To improve patients’ adherence to interventions, electro-acupuncture will be performed by acupuncturists with over 5 years of clinical acupuncture experience and obtained a license from the Ministry of Health of the People’s Republic of China. Before performing the treatment, acupuncturists will receive centralized training including an introduction to the basic clinical research methods and a practical demonstration of the treatment. WeChat will also be used for making appointments and regular reminders. At each part of the study, including assessing ovarian function before and after the intervention, performing electro-acupuncture, or making follow-up visits, the independent gynecologist will make appointments and remind participants of some notes by using this APP.

The treatments of both two groups start after a spontaneous period or a withdrawal bleeding by progestin. For patients with amenorrhea or oligomenorrhea, the withdrawal bleeding is induced using progesterone by the outpatient doctors, and then the intervention starts after the withdrawal bleeding. The acupuncture protocols are formulated according to the theory of traditional Chinese medicine. The number of needles used, methods of stimulation (manipulation and electro-acupuncture), frequency, and time of the treatment are detailed described following the CONSORT and STRICTA recommendations [10].

Fixed protocols are used for both the treatment group and the control group. All patients receive the treatment of active acupuncture or sham acupuncture, twice or three times a week with a maximum of 24 times in 8-12 weeks. Treatments will not be performed during menstruation in both two groups. The treatment date, time, the name of the acupuncturist and the intensity of the electro-acupuncture stimulation which can vary between the different electrodes are recorded when the patient receives acupuncture treatment. The range of the intensity of the electro-acupuncture stimulation will be recorded, e.g., 1.2–3.0 mA.

#### Treatment group:

For the treatment group, two groups of acupoints will be used alternatively.

The first group consists of governor vessel (GV) 20, conception vessel (CV) 6, CV 3, bilateral stomach (ST) 29, bilateral spleen (SP) 6, bilateral ST 36, and bilateral pericardium (PC) 4. The patients will be asked to stay in a supine position and keep the whole body relaxed and comfortable. Disposable sterilized needles (size: 0.25 × 40/50 mm) will be inserted into a depth of 15~35 mm and stimulated manually to evoke needle sensation (“Deqi” in traditional Chinese medicine, TCM). And then CV 3 and CV 6, bilateral ST29, and SP6 and SP 9 bilaterally will be thereafter connected to electrical stimulators (Export Abteilung, Schwa-Medico GmbH, [name]) and stimulated with low-frequency of 2 Hz, 0.3 ms pulse length for 30 min. The intensity was adjusted to the maximum tolerated intensity of the patients. The other needles without electrical stimulators will be manually stimulated to evoke “Deqi” every 10 min.

The second group of acupoints consists of the bladder (BL) 23 and 32 bilaterally, bilateral kidney (KI) 3 and SP 6, and GV 20. Patients will be asked to stay in a prone position and keep the whole body relaxed and comfortable. GV 20 will be punctured obliquely, and other acupoints will be perpendicularly needled into a depth of 15~35 mm using disposable sterilized needles (size: 0.25 × 40/50 mm). All acupoints will be stimulated manually to evoke needle sensation (“Deqi” in TCM). And then BL 23 and 32, and KI 3 and SP 6 bilaterally will be stimulated with low-frequency in the same way as the first group. GV 20 will be stimulated manually to evoke “Deqi” every 10 min.

#### Control group

For the control group, four pseudo-acupoints are used, with two points on each shoulder and the two on each upper arm, which are not located on any meridians. The patients will be asked to stay in a supine position and keep the whole body relaxed and comfortable. Disposable sterilized needles (Size: 0.18 × 25 mm) will be inserted superficially to a depth of < 5 mm without any manual stimulus and the needle sensation (“Deqi” in TCM) should not be evoked. Electrodes are connected to the needles, but the stimulators should be turned on at an intensity of zero. Each intervention lasts for 30 min.

#### IVF-ET treatment

After the acupuncture treatment, patients’ ovarian reserve function will be evaluated again, and then IVF-ET cycle treatment will be conducted. This will be performed by the reproductive medicine center according to the patients’ situation and the standard procedure.

### Concomitant treatments

Drugs and other treatments, which may interface the evaluation of electro-acupuncture effect, will be discouraged. Discouraged treatments include sexual hormones, contraceptives, and herbs. If treatment not recommended in this trial has already been performed, relevant information should be recorded in the patient’s case report form.

### Outcome measures

#### Primary outcome measure

The primary outcome is clinical pregnancy rate per cycle of IVF-ET after acupuncture (through study completion, an average of 1 year). Clinical pregnancy was defined by the presence of a fetal heartbeat at 6–7 weeks of pregnancy. The clinical pregnancy rate is the number of clinical pregnancies per embryo transfer cycles.

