##### Outcomes of IVF

Outcomes of IVF include:
Gn dosage and usage days;E2 level and endometrial thickness on human chorionic gonadotropin (HCG) day;Number of oocytes;MII oocytes;Normal fertility rate;The number of available embryos;Number of high-quality embryos;Cycle cancelation rate (including cycle cancelation rate caused by various reasons);Implantation rate: including fresh periodic implantation rate, per cycle implantation rate and cumulative implantation rate;Fresh cycle clinical pregnancy rate and cycle cumulative clinical pregnancy rate;Early, mid, and late pregnancy abortion rate;Risk of ovarian hypertrophy and incidence of obstetric complications;FSH, LH, E2, and AMH in follicular fluid; oxidative stress-related indicators such as reactive oxygen species (ROS), superoxide dismutase (SOD) level, etc.;Live rate: including fresh cycle live rate, cycle live rate and cumulative live rate.

These outcomes will be assessed through study completion, at an average of 1 year.

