### Criteria for discontinuing interventions

Acupuncture will be ended if participants meet any of the following conditions: (1) serious adverse events occurred during or after treatment, (2) misdiagnosed after randomization, and (3) patients found to be pregnant after randomization.

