### Statistical methods

All analyses will be based on the intention-to-treat principle. Data analysis will be performed by an independent statistician using SAS statistical software (version 9.4; SAS Institute Inc.).

The analysis of variance (ANOVA) will be used to test the difference of clinical pregnancy rate (primary outcome) between the two intervention groups with the baseline date as a variate and taking into account the multicenter effect. Missing data will be imputed using the multiple imputation method. Continuous data will be presented as the mean and standard deviation, or the median and interquartile range. Categorical data will be presented as the number and percentage. Comparisons between groups will be analyzed using an independent *t* test or Wilcoxon rank-sum test for continuous variables, and a chi-square test or Fisher exact test for categorical variables. All statistical tests will be two-sided, and *p* < 0.05 will be considered statistically significant.

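### The primary outcome is defined per embryo-transfer cycle, which leaves out randomised women who never reach transfer and contradicts the stated intention-to-treat analysis

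*Protocol article*

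**What the plan says.** Primary outcome measure first names the outcome: "The primary outcome is clinical pregnancy rate per cycle of IVF-ET after acupuncture (through study completion, an average of 1 year"). Two sentences later it fixes the denominator: "The clinical pregnancy rate is the number of clinical pregnancies per embryo transfer cycles". Neither sentence restricts the outcome to a woman's first cycle.

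The unit of randomisation is the woman (Randomization and masking): "Three hundred thirty-eight participants will be randomly allocated to the treatment group and control group in a 1:1 ratio". Acupuncture then runs for 8–12 weeks, and IVF-ET follows (Interventions; IVF-ET treatment).

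Outcomes of IVF lists oocyte numbers, available embryos and "Cycle cancelation rate (including cycle cancelation rate caused by various reasons") as secondary outcomes, so cycles that stop before transfer are expected. The same list includes "Fresh cycle clinical pregnancy rate and cycle cumulative clinical pregnancy rate". Criteria for discontinuing interventions also foresees "patients found to be pregnant after randomization".

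Statistical methods states: "All analyses will be based on the intention-to-treat principle". Nowhere does the article say that a woman without a transfer counts as not pregnant.

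**The concern.** A rate per transfer is conditional on reaching transfer. In this trial that step comes after randomisation and after the whole course of treatment. It depends on oocytes and embryos, which the treatment is meant to improve. The women eligible under Inclusion criteria have low ovarian reserve or a previous poor response, so failure to reach transfer is foreseeable.

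If the arms differ in the share reaching transfer, the women compared are no longer the groups that were randomised. Benefit gained by bringing more women to transfer is left out of the rate. If those additional women have a poorer prognosis, the benefit can even lower it.

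There is also a mismatch of units. The sample size counts women and uses a formula for two independent proportions, while the outcome counts transfer cycles over an open window averaging one year.

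**Working it through.** **1. The plan's own figure (Sample size).** Inputs: 15% against 30% (the increase of 15% read as absolute), two-sided α = 0.05, power 80%, 1:1 allocation, 20% dropout.

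- Printed formula: (0.15×0.85 + 0.30×0.70)×(1.960 + 0.842)²/0.15² = 117.7, so 118 per group.
- Pooled-variance formula: 121. With continuity correction: 134, close to the stated 135.
- Dropout: 135/0.8 = 168.75, rounded up to 169; 2×169 = 338, as stated.

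So 338 follows from 135, and 135 is nearly reproduced by the continuity-corrected version but not by the printed formula. That is a separate matter. What counts here is that 135 and 338 are numbers of women, while the 15% is described as a rate per cycle.

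**2. Effect of the denominator.** Per-transfer rate = per-woman rate ÷ share reaching transfer (one transfer per woman). The protocol gives no shares, so those below are assumptions.

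| Share reaching transfer (control, treatment) | Per woman | Per transfer |
|---|---|---|
| 60%, 80% | 12% vs 12% | 0.12/0.60 = 20.0% vs 0.12/0.80 = 15.0% |
| 60%, 80% | 0.20×0.60 = 12% vs 0.20×0.80 = 16% | 20% vs 20% |
| 70%, 80% | 12% vs 12% | 17.1% vs 15.0% |
| 70%, 60% | 12% vs 12% | 17.1% vs 20.0% |

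Equal results per woman can look like harm or benefit, and a real difference per woman can vanish.

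**3. Effect of the repair on power.** If 15% and 30% are already per-woman rates, nothing changes: power with 135 per group is 84% (pooled formula). If they are per-transfer rates and a share t of women in both arms reaches one transfer, the per-woman rates are 0.15t and 0.30t. Power = Φ{[d√n − 1.96√(2p̄(1−p̄))]/√(p₁(1−p₁) + p₂(1−p₂))}, where d = p₂ − p₁ and p̄ is the mean of p₁ and p₂:

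| t (assumed) | Per-woman rates | Power, 135 per group | Power, 169 per group | n per group for 80% |
|---|---|---|---|---|
| 0.9 | 13.5% vs 27% | 79% | 87% | 138 |
| 0.8 | 12% vs 24% | 73% | 82% | 160 |
| 0.7 | 10.5% vs 21% | 66% | 76% | 188 |
| 0.6 | 9% vs 18% | 58% | 68% | 226 |

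The 169 column applies only if every randomised woman has a known outcome.

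**4. Several cycles per woman.** This was simulated under no treatment effect: 135 women per group, 80% reaching transfer, a 15% rate, within-woman correlation 0.1–0.3, and all transfers tested as independent (5,000 runs per setting; all inputs except 135 and 15% assumed). If transfers stop at pregnancy, type I error is 5.1–5.6% with up to two or three transfers. The expected rate then drifts from 15% to about 13–14% at correlation 0.2–0.3, because women who fail contribute more transfers. If transfers continued after pregnancy, type I error would be 5.6–7.3% with up to two and 6.6–9.1% with up to three.

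**The case against.** The strongest reply is that the article does not say women contribute several cycles. IVF-ET treatment can be read as describing one cycle after acupuncture, the cumulative rate is listed separately as secondary, and the one-year phrase may only describe follow-up. This stands: repeated counting is left open, not planned. A reader might infer a seriously inflated type I error, but the documents do not support that. Where transfers stop at pregnancy, the error stays near 5%.

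A reader might also infer that the randomised comparison is lost or its sign reversed. A reversal can be constructed. Suppose 70% of controls reach transfer and 15.0% conceive (21.4% per transfer). In the treated arm 85% reach transfer, and the additional 15% conceive at 10%. Then 0.150 + 0.15×0.10 = 16.5% of treated women conceive, but only 0.165/0.85 = 19.4% per transfer. That rests on an assumed effect of 1.5 points. At the planned effect with the same shares, 15% against 30% per woman becomes 21.4% against 35.3% per transfer, in the same direction. The bias is real in kind and unknown in size.

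Nor does the article support the inference that women without a transfer will be given imputed pregnancies. It says only "Missing data will be imputed using the multiple imputation method". Such a woman's result is known, and under the printed definition she is outside the denominator.

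Loss of power under the present definition cannot be asserted either. Sample size does not say whether women without a transfer belong to the 20% dropout allowance. If they do, 80% of 169 is still 135.

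None of these replies touches the conflict between the transfer denominator and intention to treat.

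**Conclusion.** The point holds as an inconsistency in what the article fixes. The outcome carries two denominators, and the one given as its definition excludes randomised women on a post-randomisation result that the treatment may change. This does not depend on how many cycles a woman has, on the imputation rule, or on how conceptions before IVF are handled.

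The size of the bias cannot be derived from the documents. In the illustrations it is zero when the arms have equal shares reaching transfer and no true effect, and it reaches 5 percentage points when the assumed shares differ by 20 points. The uncertainty over cycles per woman is secondary. Because the primary comparison is affected, the definition should be corrected before unblinding.

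**What to change.** Define the primary outcome as clinical pregnancy (fetal heartbeat at 6–7 weeks) per randomised woman, one observation each, from the first IVF-ET cycle started after acupuncture. Count a cancelled cycle or no transfer as not pregnant. State before unblinding how conception before IVF is counted; Criteria for discontinuing interventions only ends acupuncture for these women. Keep the per-transfer and cumulative rates as secondary outcomes. Use the same denominator in Primary outcome measure, Sample size and Statistical methods.

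Cost: no new data are needed, since pregnancy, cancellation and follow-up are already recorded. The change does alter the definition of a registered primary outcome during recruitment, so it must be documented as an amendment. The headline rate will be lower than the per-transfer rate. The sponsor must also state whether 15% and 30% are per-woman or per-transfer rates. If per-woman, the sample size is unchanged. If per-transfer, the stated power has to be restated using the table above and an explicit assumption about the share reaching transfer.
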